### Objectives

The main purpose of this study is to identify whether exercises with mindfulness elements carried out at the beginning of individual therapy sessions help to improve the therapeutic process under effectiveness conditions. Consequently, we designed a study to analyze the effects of a 5-min session-introducing intervention with mindfulness elements (SIIME) conducted together by trainee therapists and their patients in a randomized, controlled, longitudinal design under naturalistic conditions with PMR as the active control group.

More specifically, we will examine the effects of SIIME practiced by both outpatients and CBT trainee therapists at the beginning of the 25 therapy sessions (brief-term CBT of the German healthcare system) on (a) therapeutic alliance measured on a session-to-session basis and (b) on clinical outcomes assessed every 10 sessions. Thus, before the start of therapeutic treatment, patients are randomized into a treatment-as-usual + mindfulness intervention group (TAU + M) practicing SIIME, a TAU + PMR-control group practicing a session-introducing short form of PMR, or a TAU control group without standardized session-introducing intervention. Before the start of the intervention study, all therapists will participate in a 6-week workshop-based mindfulness and PMR program. We will investigate the following hypotheses:We hypothesize that both patients and therapists of the TAU + M will experience higher levels of therapeutic alliance compared to the TAU + PMR and TAU.We hypothesize that in the TAU + M, there will be stronger reductions in clinical symptomatology of patients compared to the TAU + PMR and TAU.

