### Primary outcome measures

Primary outcome measure 1: To assess the quality of the therapeutic alliance, we will apply the Working Alliance Inventory- Short Revised (WAI-SR; (Hatcher and Gillaspy 2006)). The WAI-SR is a 12-item self-report instrument with patient and therapist perspectives rated on a seven-point scale. It includes three subscales: bond, goals, and tasks. The bond subscale reflects the emotional relationship between patient and therapist. The goals and tasks subscales refer to the agreement of patients and therapists concerning the treatment goals and tasks. The WAI-SR is considered the gold standard for alliance assessment, has excellent psychometric properties, and is outcome predictive, as has been demonstrated in meta-analyses (e.g. (Horvath et al. 2011)).Primary outcome measure 2: To assess general symptom severity, the Global Severity Index (GSI) of the Brief Symptom Checklist (BSCL; (Derogatis and Melisaratos 1983; Franke 2000)) will be applied. The BSCL is the short version of the Symptom-Checklist-90-Revised (SCL-90-R; (Derogatis and Lazarus 1994)) and consists of 53 items forming nine subscales as follows: somatization, obsessive-compulsive, interpersonal sensitivity, depression, anxiety, hostility, phobic anxiety, paranoid ideation, and psychoticism, which are rated on a five-step scale. It showed excellent internal consistencies, with 0.71 ≤ α ≤ 0.85; good retest reliabilities, with 0.68 ≤ *r* ≤ 0.91; high correlations to the original SCL-90-R, with 0.92 ≤ *r* ≤ 0.99; and good construct validity, with scale-outcome correlations between 0.30 ≤ *r* ≤ 0.72.

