### Secondary outcome measures

To assess general depressive symptoms of the patients, we will apply the Beck Depression Inventory-II (BDI, (Hautzinger et al. 1994; Beck et al. 1996)), a screening instrument for depression derived from the criteria of the DSM-IV (American Psychiatric Association 2000) that consists of 21 items on a four-step scale. It revealed an internal consistency of *α* = 0.88, a split-half reliability of *r* = 0.72, a retest reliability of *r* = 0.75, and convergent validities of 0.71 ≤ *r* ≤ 0.89.To assess general anxiety symptoms of the patients, we will apply the Beck Anxiety Inventory (BAI; (Beck et al. 1988; Margraf and Ehlers 2007)), which consists of 21 items. It revealed an internal consistency of *α* = 0.90, a split-half reliability of *r* = 0.70, a retest reliability of *r* = 0.75, and convergent validities of 0.50 ≤ *r* ≤ 0.61.To assess interpersonal functioning, we will apply the short version of the Inventory of Interpersonal Problems (IIP), which is a 32-item instrument with a circumplex structure (Horowitz et al. 1988). It consists of eight factors that are rated on a five-step scale: domineering, intrusive, overly nurturant, exploitable, nonassertive, socially avoidant, cold, and vindictive. It has excellent psychometric properties, with 0.75 ≤ α ≤ 0.94. The criterion validity of the measure has been demonstrated via correlations to the SCL-90-R with 0.07 ≤ *r* ≤ 0.75.To assess therapists’ views on the psychological, social, and occupational functioning of the patients, we will apply the Global Assessment of Functioning (GAF). This 100-point scale is divided into sections, each with ten points. The ten-point intervals have anchor points (verbal instructions) describing symptoms and functioning, while the 1–10 interval describes the most severely ill and the 91–100 interval describes the healthiest patient. The GAF is broadly acknowledged and has been applied worldwide in hundreds of studies (Aas 2010).To assess therapist variables, we will apply items of the Development of Psychotherapists Common Core Questionnaire (DPCCQ; (Orlinsky and Ronnestad 2005)). The full DPCCQ consists of 370 questions, and its psychometric properties have been demonstrated in a sample of about 5000 therapists (Orlinsky and Ronnestad 2005). We will apply the subscales of the instrument that have been found to be predictive of therapeutic processes and outcomes in several studies: difficulties in practice, warm interpersonal style, advanced relational skills, personal satisfaction, and personal burdens (Nissen-Lie et al. 2014).To assess general change mechanisms, we will apply the Scale for the Multiperspective Assessment of General Change Mechanisms in Psychotherapy (SACiP; (Mander et al. 2013)). The SACiP is a measure with six dimensions: resource activation; problem actuation; mastery; clarification of meaning; emotional bond, with three items each; and agreement on collaboration, which comprises the aspects of tasks and goals, with six items. The measure demonstrated an excellent factor structure (with 0.51 ≤ λ ≤ 0.85), revealed good internal consistencies (with 0.71 ≤ α ≤ 0.90), and was outcome predictive.To assess patients’ and therapists’ general development of mindfulness over the course of the study, we will apply the Kentucky Inventory of Mindfulness Skills (KIMS). The KIMS (Baer et al. 2004) is based on the conception of mindfulness described in dialectical behavior therapy (Linehan 1993a; Linehan 1993b) and addresses four aspects: observing, describing, acting with awareness, and accepting without judgment, with 39 items that are rated on a five-step scale. The EFA revealed an excellent factor structure with factor loadings of 0.41 ≤ λ ≤ 0.86; excellent internal consistencies, with 0.83 ≤ α ≤ 0.91; and is outcome predictive (Baer et al. 2004). Several studies replicated the four-subscale structure of the KIMS by means of factor analyses (e.g. (Ströhle et al. 2010; Baum et al. 2010)).

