### Statistical analysis

We will compare baseline descriptive statistics between the three study arms with *χ*^2^-tests (for categorical variables) and with ANOVA / t-tests (for continuous variables).

In line with the recommendations of Baldwin, Imel, Braithwaite, and Atkins (Baldwin et al. 2014), we will apply a multilevel modeling approach to address the nested data structure (sessions at level 1 are nested within patients at level 2, which are nested within therapists at level 3): Thereby, we will treat time as a within-subject factor and treatment condition as a between-subject factor. We will analyze main effects, that is, differences in intercepts of TAU + M versus TAU + PMR versus TAU concerning process and outcome variables, and interactive effects, that is, differences in slopes of TAU + M versus TAU + PMR versus TAU concerning process and outcome variables (Raudenbush and Bryk 2002). Our statistical hypothesis implies that the intercept is significantly higher in the TAU + M than in the TAU + PMR and the TAU concerning both the process and outcome variables. Additionally, it implies that the slope increases significantly stronger in the TAU + M than in the TAU + PMR and the TAU concerning both the process and outcome variables. We will conduct analyses on the intention-to-treat sample as well as on the completer sample. Furthermore, patients’ and therapists’ pre-treatment characteristics will be investigated as outcome predictors at levels 2 and 3 to control for differential effects on outcome in the three treatment arms.

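### The statistical hypothesis states one direction for all outcomes, which is reversed for the symptom scales, including primary outcome 2, and contradicts hypothesis 2

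*Protocol article*

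**What the plan says.** Objectives gives two hypotheses with opposite signs. For alliance, patients and therapists in TAU + M "will experience higher levels of therapeutic alliance compared to the TAU + PMR and TAU". For symptoms, "in the TAU + M, there will be stronger reductions in clinical symptomatology of patients compared to the TAU + PMR and TAU".

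The Statistical analysis section puts both into one statistical form with a single sign. On levels, the "intercept is significantly higher in the TAU + M than in the TAU + PMR and the TAU concerning both the process and outcome variables". On change over time, the "slope increases significantly stronger in the TAU + M than in the TAU + PMR and the TAU concerning both the process and outcome variables". Neither sentence makes an exception for any scale.

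The second primary outcome is a severity measure: "To assess general symptom severity, the Global Severity Index (GSI) of the Brief Symptom Checklist". Among the secondary outcomes, the BDI-II ("To assess general depressive symptoms of the patients, we will apply the Beck Depression Inventory-II") and the BAI measure symptoms, and the IIP measures interpersonal problems. The article mentions no reverse scoring.

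**The concern.** On a severity score, a higher intercept means more symptoms, and a more strongly increasing slope means symptoms that get worse, or improve less, than in the controls. Hypothesis 2 predicts the opposite. The analysis section therefore contradicts the objective that it is meant to put into statistical terms, and it does so for a primary outcome.

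What is at stake is the prespecified rule for what counts as support. Taken as written, the section would treat symptom benefit in TAU + M as failing to confirm the hypothesis and would point to symptom worsening as the predicted direction. An analysis plan that carried this sentence over would inherit the error.

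**Working it through.** The point is one of sign, so the main check sets the statements side by side. The article gives no figure of its own to reproduce here.

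**Step 1: do the outcome variables include the symptom scales?** Yes. Objectives separates session-by-session alliance from effects "on clinical outcomes assessed every 10 sessions", and the Statistical analysis section names process and outcome variables together. Alliance alone cannot be meant.

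**Step 2: compare signs.** Let Δ be the slope in TAU + M minus the slope in a control arm.

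| Scale | A high score means | Δ under Objectives | Δ under Statistical analysis |
|---|---|---|---|
| WAI-SR | stronger alliance | above 0 (hypothesis 1, as levels) | above 0 |
| GAF | healthier | not stated; benefit is above 0 | above 0 |
| KIMS | more mindfulness skill | not stated; benefit is above 0 | above 0 |
| BSCL-GSI (primary 2) | more severe | below 0 (hypothesis 2) | above 0 |
| BDI-II, BAI | more symptoms | below 0 (hypothesis 2) | above 0 |
| IIP | more problems | not named in hypothesis 2; benefit is below 0 | above 0 |

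The GAF direction is stated in the article. For the KIMS, BDI-II, BAI and IIP it is inferred from what the article says each scale measures.

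**Step 3: the intercept.** Table 1 gives the BSCL, BDI-II, BAI, IIP, GAF and KIMS a Pre wave; the WAI-SR is collected only at sessions 1–25. If time is coded zero at Pre, the intercept contrast on the first six is a pre-treatment difference. Its expectation is zero under randomisation, so it is not an effect of the exercise in either direction. The article does not state the time coding, so this part is conditional.

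**Step 4: an illustration of the literal reading.** Assumptions, not taken from the article: 50 analysed per arm (150/3, no dropout), unit variance, equal correlation r between waves, linear divergence from zero at Pre, waves at sessions 0, 5, 15 and 25, and significance at |z| > 1.96.

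- Mean wave time = (0 + 5 + 15 + 25)/4 = 11.25.
- Sxx = 126.5625 + 39.0625 + 14.0625 + 189.0625 = 368.75.
- SE(Δ) = √[(2/50) × (1 − r)/368.75], which is 0.00736 at r = 0.5.
- For a benefit of 0.5 SD by session 25, |Δ| = 0.5/25 = 0.02 and |z| = 0.02/0.00736 = 2.72.
- Probability of a significant result in the direction of hypothesis 2: Φ(2.72 − 1.96) ≈ 0.78 (0.58 at 0.4 SD, 0.90 at 0.6 SD).
- Probability of a significant result in the direction stated in Statistical analysis: Φ(−2.72 − 1.96) ≈ 1.5 × 10⁻⁶.
- At r = 0.05, the correlation printed in the power paragraph: SE = 0.01015 and |z| = 1.97. The two probabilities are about 0.50 and 4 × 10⁻⁵.

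Whichever r is used, a real benefit of this size has practically no chance of meeting the criterion as worded, even for one slope contrast.

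**Step 5: what does not change.** The power analysis is for a repeated-measures interaction among three groups, an omnibus test without direction. Reversing the sign of a hypothesis alters neither that test nor the sample size.

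**The case against.** The best defence is that this is loose drafting with no analytic consequence. The sentence looks written for alliance and then extended to outcomes in general. It is introduced as what the hypothesis implies, so Objectives governs, and Objectives is clear about symptoms. The planned analyses are described as differences in intercepts and slopes, no one-sided test is stated, and the power analysis is omnibus.

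Most of this stands. Two-sided or omnibus p-values and estimates are the same under either wording, and a careful analyst would probably recover the intended direction. It does not remove the contradiction. A slope that increases more strongly might be read as one that changes more in the favourable direction, but "Our statistical hypothesis implies that the intercept is significantly higher in the TAU + M" has no such reading for a severity score.

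A reader might go further in three ways that the documents do not support.

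- *That the direction of the claim is left open until the data are seen.* It is not: Objectives fixes it for symptoms.
- *That worsening under TAU + M would readily be declared a success.* The 0.78 in the working also applies, by symmetry, to one slope contrast against one control under a 0.5 SD worsening. The statistical hypothesis asks for a higher intercept as well as a steeper slope, against both controls. Under the same assumptions at r = 0.5, with the same worsening against both controls, the slope part against both has probability about 0.65, and the full criterion about 0.001.
- *That the intercept hypothesis is certainly a test of baseline.* The section equates intercept differences with main effects, which could mean an average level. The baseline reading depends on a time coding that the article does not give and may properly leave to the SAP.

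**Conclusion.** The concern holds as an error in the stated criterion for support. For primary outcome 2 and three secondary scales (BDI-II, BAI and IIP), the direction in the Statistical analysis section is the opposite of benefit, and it contradicts hypothesis 2. Read literally, a true symptom benefit cannot satisfy the statistical hypothesis on these scales. The direction is right for WAI-SR, GAF and KIMS.

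The conclusion rests on the scales being scored as their descriptions imply and on the absence of any reverse scoring in the article. It does not depend on the illustrative effect sizes or correlations. Estimates, two-sided or omnibus p-values and the sample size are unaffected; only a one-sided test run as worded would change the inference. The intercept point is an additional fault only if time is coded zero at Pre.

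**What to change.** Replace the two directional sentences in the Statistical analysis section with directions by scale:

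- For BSCL-GSI, BDI-II, BAI and IIP, the slope over sessions is more negative in TAU + M than in each of TAU + PMR and TAU.
- For WAI-SR, GAF and KIMS, keep the positive direction.
- State that tests are two-sided, and that a significant difference towards higher symptom scores in TAU + M is reported as worsening and not as support.
- State where time is zero. If it is at Pre, drop the intercept hypothesis for every measure with a Pre wave, which includes GAF and KIMS. If it is placed elsewhere and a level hypothesis is kept, the direction on the symptom and problem scales must be lower, not higher.

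The cost is a few sentences in the protocol or SAP before analysis. No data collection, sample size or procedure changes.

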## Discussion

Mindfulness, a specific form of attention that is non-judgmental, purposeful, and focused on the present moment, has its origins in an Eastern Buddhist tradition that is over 2500 years old (Cigolla and Brown 2011) and is currently well established in CBT (Kabat-Zinn 1990; Grossman et al. 2004). Usually, mindfulness interventions have been investigated in a structured, manualized group setting (Bohlmeijer et al. 2010). However, an increasing demand to investigate the effects of SIIME practiced together by patients and trainee therapists in individual therapy under effectiveness conditions has been highlighted, because this could elucidate opportunities to improve clinical training (e.g. Ryan et al. 2012; Bruce et al. 2010; Dunn et al. 2013; Grepmair et al. 2007). Furthermore, only a few studies have compared mindfulness interventions with an active control group, and most of the investigations that did were conducted with non-clinical samples. Most of these studies applied PMR as an active control group and demonstrated beneficial effects of mindfulness (e.g. Feldman et al. 2010; Semple 2010). Consequently, we designed the PrOMET study to analyze the effects of brief SIIME conducted by both trainee therapists and their patients at the beginning of individual therapy sessions in a randomized, controlled, longitudinal design under effectiveness conditions with TAU + PMR and TAU as control groups.

### Innovative aspects of the PrOMET study

With the PrOMET study, we intend to address four innovative aspects of effectiveness research: First, concerning the therapy session, our study is one of the first to investigate effects of different rituals of session introduction (TAU + M versus TAU + PMR versus TAU) in individual psychotherapy. Second, concerning the training of psychotherapists, we want to create direct intersections between workshop theory and practical clinical training by directly implementing mindfulness and PMR elements from the workshop training into individual therapy sessions of trainees and then investigate them in our research design. Third, concerning research strategies, we intend to combine in our naturalistic study elements from process-outcome research with aspects from the research designs of randomized, controlled trials. Fourth, concerning mindfulness, we will transfer elements of mindfulness that are traditionally investigated in group-therapy settings to individual therapy and investigate them scientifically.

### Aspects concerning bias minimization

In our nested study design, we will investigate patient and therapist contributions concerning the effects of the interventions. In contrast to double-blind medical trials, patients and therapists are informed about the different intervention groups and will actively participate in the study plan because they perform the interventions actively by themselves. This active integration of participants into the treatment plan should not be regarded as bias but rather as an important aspect of the successful implementation of psychotherapeutic interventions and as a necessary condition to implement the study design (Flückiger 2014). We will investigate the intensity of the active involvement of participants by asking specific questions concerning mindfulness and PMR experiences during the session and mindfulness and PMR practice at home and then statistically control these aspects as manipulation checks. Additionally, we will apply an allegiance scale that addresses positive and negative attitudes towards all three treatment conditions. The allegiance scale will be completed by patients and therapists and then used to control for potential bias effects of specific attitudes.

#### Bias minimization, patient

An experienced research psychotherapist who is not involved in the study will randomly assign patients to the three different treatment conditions to reduce the potential biases of participant characteristics. All researchers and participants of the study are blind to the randomization process. Furthermore, the specific inclusion and exclusion criteria define relatively homogenous groups. Additionally, comorbidities with other psychiatric disorders, age, sex, prior experiences with mindfulness and PMR techniques, and the intensity of the current mindfulness and PMR practice will be tested as potential confounding variables. A potential limitation is that it is not possible to blind the participants concerning the different treatment groups because they will know which treatment condition they are randomized to according to the specific intervention they receive during the therapy sessions. However, this is a typical limitation of most psychotherapy studies with a randomization process (Flückiger 2014). We addressed this issue, as described above, according to the revised CONSORT statement (Zwarenstein et al. 2008; Altman et al. 2001).

#### Bias minimization, therapist

The allegiances of therapists to the mindfulness or PMR approaches could be a potential bias (Munder et al. 2012). We will try to minimize this bias by randomizing patients (and not therapists) to the different treatment conditions in a crossed-therapist design (Falkenstrom et al. 2013). Consequently, each therapist potentially treats patients under all treatment conditions, since it is likely that different patients treated by the same therapist will be randomized to different treatment conditions. Additionally, we will apply an allegiance scale as described above. Therefore, allegiance biases will be statistically controlled. However, our sample size does not allow a perfect control for this effect. Consequently, it has to be noted as a potential limitation of the generalizability of the study results. Additionally, prior experiences with mindfulness and PMR techniques, as well as the intensity of the current mindfulness and PMR experience and practice with patients in therapy sessions, will be tested as potential confounding variables.

## Conclusion

In our study, we will investigate the effects of SIIME conducted by trainee therapists and their patients at the beginning of individual therapy sessions in a randomized, controlled, longitudinal design under effectiveness conditions with TAU + PMR and TAU as control groups. The study results could have important practical implications because they could inform ideas about how to improve the training of psychotherapists in outpatient training centers that could be implemented very easily, especially since there is no need for complex infrastructures or additional time concerning these brief SIIME that are directly implemented in the treatment sessions.

